## Methods and analysis

2

### Study design

2.1

The MOVESCHOOL was a quasi-experimental study (trial registered on Clinicaltrials.gov: NCT06254638). This work was the protocol for the implementation of a school-based multicomponent intervention in the experimental group with pre- and post-intervention measures. MOVESCHOOL was a multi-center intervention whose management was designed to ensure effective collaboration and communication between the research groups. The research groups were composed of qualified researchers and graduates in PA and Sport Sciences from two universities [University of Extremadura (UEX) and University of Cadiz (UCA), Spain]. Both research groups followed a uniform study protocol for training, fieldwork, data collection and management, and quality control procedures. Continuous telematic communication was maintained throughout the study. A graphical summary of the study can be seen in the Supplementary file.

### Participants and selection criteria

2.2

Participants in the MOVESCHOOL study were apparently healthy adolescents from secondary schools in the regions of Caceres and Cadiz (Spain). The MOVESCHOOL study established the following inclusion criteria for participants: (i) enrolled in 7th or 8th grade (12–14 years old); (ii) without any physical disabilities or health issues that could restrict PA levels; and (iii) having parental or legal guardian consent to participate in the study. Additionally, we included three criteria for schools: (i) having at least 60 students in 7th and 8th grade; (ii) not involved in any other PA or health promotion programs; and (iii) located within a 50-kilometre radius of the research group’s centers in Cadiz and Caceres.

Figure 1 illustrates the flow diagram of the participants recruitment process. Seven schools in Caceres and four schools in Cadiz were selected to participate through a letter of invitation addressed to the school administration. A meeting was held with the school management teams of the selected schools, to explain the study and obtain their consent. Two study groups were established through a nonequivalent control group design: (i) intervention group and (ii) control group. In Cadiz, two intervention groups and two control groups were assigned; and in Caceres, three intervention groups and four control groups were assigned. Each group corresponds to a different school. All 7th and 8th grade students at the participating schools who provide their informed consent were invited to participate in the study. The parents of these students received an information document detailing the study, the inclusion criteria, the informed consent process, and an invitation to attend an information meeting at the school. For students to participate in the study, their parents or guardians had to sign the informed consent form along with the student’s consent.

**Figure 1 fig1:**
[figure not shown]
Flow diagram of study participants.

The recruitment process was designed to achieve 800 participants (400 per group), which guarantees to detect small sized effects with an *α* error of 0.001 and a power (1 − *β*) of 0.95, even with an experimental dropout rate of 15% (GPower 3.1.9.4, Düsseldorf, Germany). To establish this sample size, Love et al. (38) were referenced, as they found an average effect size <0.1 for our main variable, MVPA time during the school day.

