**Methods:**

A quasi-experimental study was conducted with the aim to involve a total of 800 students aged 12–14 years old from 11 schools (7th and 8th grade) in south-western Spain, five schools forming the intervention group and six schools forming the control group. The evaluation included two independent measurements: pre-intervention and post-intervention. The intervention lasted 29 weeks and consisted of a multi-component programme including a weekly PAL, two 5 min daily AB, and a daily AR. Primary outcomes included accelerometer-based PA and sedentary time, health-related physical fitness, academic indicators, and executive functions. For statistical analyses, descriptive, correlational, regression, and repeated measures ANOVA analyses will be applied. Additionally, qualitative data were gathered through semi-structured individual interviews and focus groups, and information will be evaluated with thematic analysis.

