##### Physical activity and sedentary time

2.5.1.1

The Actigraph device (Actigraph GT3X+, Inc., Pensacola, FL, United States) was utilized for assessing PA at different intensities (light, moderate and vigorous) and sedentary time throughout the entire day. Participants were instructed to wear the monitor on their non-dominant wrist for eight consecutive days. Participants were advised to wear the accelerometer throughout the day (including sleeping time), except during aquatic activities or situations where exposure to water is possible. The screening and data collection procedures adhered to established protocols employed in previous research involving adolescents populations (42). Data will be extracted and analyzed using the GGIR package. Inclusion criteria for the analyses consist of: (i) a minimum of 3 valid weekdays of data and at least 1 valid weekend day of data; (ii) a minimum recording duration of 10 h per day (42, 43). The power analysis is performed based on MVPA during the school day, as it is the main variable of the study.

Additionally, to gather information on screen time throughout the day and the devices used, screen time was assessed using the specific items of the Youth Leisure-time Sedentary Behaviour Questionnaire (YLSBQ) (44). This questionnaire assessed the amount of recreational time per day spent on television, video games, computers, tablets, and smartphones, separately during weekdays and weekends. The student must choose whether they spend “0 min”, “30 min”, “1 h”, “2 h”, “3 h”, “4 h” or “5 h or more” per day on each of these behaviours.

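### The sample-size statement guarantees 95% power at α 0.001 for small effects, but this holds only under an unstated effect metric and pre-post correlation, and only if allocation by whole schools is ignored

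*Protocol article*

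**What the plan says.** The sample-size statement stands in section 2.2 of the protocol article, under Figure 1. Recruitment was "designed to achieve 800 participants (400 per group), which guarantees to detect small sized effects", with a type I "error of 0.001 and a power" (1 − β) "of 0.95, even with an experimental dropout rate of 15" per cent. The calculation is attributed to GPower. The effect size rests on an earlier study, of which the article says "they found an average effect size <0.1 for our main variable, MVPA time during the school day". Section 2.5.1.1 confirms the variable: "The power analysis is performed based on MVPA during the school day, as it is the main variable of the study".

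Allocation was by school. The abstract describes "five schools forming the intervention group and six schools forming the control group", and section 2.2 says "Each group corresponds to a different school".

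Section 2.6 plans a repeated-measures analysis, with a separate model for each outcome and adjustment for gender, city and socioeconomic status. It names no school term and sets a 95% confidence level.

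**The concern.** The paragraph joins a very strict α, a high power, a modest sample and a very small cited effect, and calls the result guaranteed. Those four do not obviously fit together. It also makes no allowance for students being grouped in 11 schools, and no other section of the article supplies one.

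The stake is interpretation. Data collection ran from October 2023 to May 2024, so the sample is fixed. If the statement is left as it is, a non-significant result on school-day MVPA could be presented as the null finding of a 95%-powered study. The power actually available may be far lower.

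**Working it through.** **Inputs from the article.** 800 recruited; 15% dropout leaves 800 × 0.85 = 680 evaluable, 340 per group. α = 0.001 (taken as two-sided), power 0.95, 11 schools (5 against 6), two time points.

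**Assumed, because not given.** Pre-post correlation ρ, shown from 0.3 to 0.9. School ICC of 0.01, 0.02 and 0.05. Mean cluster size 680/11 = 61.8.

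**1. Reproducing the stated figure, schools ignored.** For the 2 × 2 group-by-time interaction in GPower's form, λ = N f² × 2/(1 − ρ), referred to a noncentral F with 1 and N − 2 df.
- f = 0.10, ρ = 0.5: λ = 680 × 0.01 × 2/0.5 = 27.2, power 0.97. The required N is about 616, or 616/0.85 = 725 with dropout, so 800 covers it.
- f = 0.10, ρ = 0.3: λ = 680 × 0.01 × 2/0.7 = 19.4, power 0.86.
- Threshold, normal quantiles: 95% power needs λ = (3.291 + 1.645)² = 24.4, so 1 − ρ = 13.6/24.4 and ρ ≈ 0.44. The noncentral F puts it marginally higher.

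In a 2 × 2 layout the interaction shifts each cell mean by a quarter of the difference in change, so f = 0.10 corresponds to a difference in change of 4 × 0.10 = 0.40 SD.

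**2. Reading the effect as a standardised mean difference, schools ignored.** n per group = 2[(3.291 + 1.645)/d]². This gives 1,218 for d = 0.2 and 4,872 for d = 0.1, against 340 evaluable. Noncentral-t power at 340 per group:

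| d | α = 0.001 | α = 0.05 |
|---|---|---|
| 0.1 | 2% | 26% |
| 0.2 | 24% | 74% |

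The effect detectable with 95% power at α 0.001 is (3.291 + 1.645) × √(2/340) ≈ 0.38 SD, for a post-only comparison or a change score with ρ = 0.5. For change scores with ρ = 0.7, 0.8 and 0.9 it is 0.29, 0.24 and 0.17 SD.

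**3. Allowing for schools in the most favourable case (f = 0.10, ρ = 0.5).** Design effect = 1 + (61.8 − 1) × ICC; λ = 27.2/design effect; error df left at the student level.

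| ICC (assumed) | Design effect | Effective N | λ | Power at α 0.001 |
|---|---|---|---|---|
| 0 | 1.00 | 680 | 27.2 | 0.97 |
| 0.002 | 1.12 | 606 | 24.3 | 0.947 |
| 0.01 | 1.61 | 423 | 16.9 | 0.79 |
| 0.02 | 2.22 | 307 | 12.3 | 0.58 |
| 0.05 | 4.04 | 168 | 6.7 | 0.24 |

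These figures do not yet charge for having only 11 schools.

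**4. What 5 against 6 schools can detect.** In SD units of change, SE = √{[ICC + (1 − ICC)/68]/5 + [ICC + (1 − ICC)/56.7]/6}, where 340/5 = 68 and 340/6 = 56.7, tested on 11 − 2 = 9 df. At ICC 0.01: SE = √{(0.01 + 0.0146)/5 + (0.01 + 0.0175)/6} = 0.097. At ICC 0.02 and 0.05 it is 0.114 and 0.155. With 95% power:
- two-sided α 0.05: 0.40, 0.47 and 0.63 SD;
- two-sided α 0.001: 0.70, 0.82 and 1.11 SD.

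**5. The two error rates.** Sizing uses α = 0.001. Section 2.6 works at 95% confidence, that is α = 0.05. The article does not connect the two.

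**The case against.** The strongest defence is that the stated power does reproduce on a natural reading. The article names GPower, says small and plans a repeated-measures analysis. With the conventional small f = 0.10 and ρ = 0.5, 680 evaluable students give 0.97. The test, ρ and the ICC are also details that an article may leave to a fuller protocol or analysis plan. Both points stand. The omissions alone would not be a finding. What remains is a numerical guarantee stated in the article, and the favourable reading survives only with students counted as independent. An ICC as small as 0.002 already takes it below 0.95.

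Three stronger readings are tempting, and the documents do not support them.

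- A reader might infer that the design detects only effects about four times the cited one. That needs the cited value to be a standardised mean difference and ρ to be near 0.5 (or a post-only comparison). The article gives neither. With ρ of 0.7 to 0.9 the ratio to 0.1 is about 2.9 to 1.7. If the value is f, the ratio at ρ = 0.5 is about 1.
- A reader might infer that, even taken as f, any value below 0.1 is out of reach. Without clustering, 680 students detect f = 0.095, 0.074 and 0.060 at ρ = 0.5, 0.7 and 0.8. Smaller values such as f = 0.05 at ρ = 0.5 (24% power) do remain underpowered.
- A reader might infer that power for the cited effect is just 2%. That is d = 0.1 at α 0.001. At the 95% level of section 2.6 it is 26% without clustering, and about 15%, 12% or 8% with the assumed ICCs and 9 df.

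The ICC range and the 9-df test are assumptions of this check and are not in the plan.

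**Conclusion.** The power statement is wrong as written, in this limited sense: 800 students do not guarantee 95% power at α 0.001 for small effects. Without clustering it depends on an unstated metric (f rather than d) and an unstated ρ of about 0.44 or more. With clustering, the best case drops to roughly 0.79 to 0.24 over an assumed ICC of 0.01 to 0.05. How far the cited effect lies below what the design can detect cannot be settled from the article, because its metric is not given. The absence of any allowance for school allocation in the stated figure, and the mismatch between the sizing α and the analysis confidence level, do not depend on that metric.

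**What to change.** Rewrite the sample-size paragraph in section 2.2:
- Delete the word that makes the power a guarantee.
- Name the test (group by time on school-day MVPA), the effect metric, the assumed pre-post correlation and the assumed school ICC.
- Use one α, consistent with section 2.6.
- Report the effect that 340 per group in 5 against 6 schools can detect over a range of ICCs. For example, this is about 0.40 to 0.63 SD of change at two-sided 0.05, 95% power and 9 df, for assumed ICCs of 0.01 to 0.05.
- State the metric of the cited average effect. If it is a standardised mean difference, say that it lies below the detectable range, so that a non-significant school-day MVPA result will be interpreted from its confidence interval.

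The cost is one paragraph and a less favourable stated power. No extra students or measurements are needed.

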### Interventions

2.3

The MOVESCHOOL study implemented a multicomponent school-based intervention over a period of 29 weeks. As we have explained in the introduction section, the study is based on the CAS framework (26). In this way, and also following the COM-B behaviour change model, the three basic elements (i.e., Capability, Opportunity and Motivation) were worked on with teachers and school leaders in a kick-off meeting, where the protocol to be followed in the project was explained to all the teachers and the staff from each school before the start of the intervention. This ensured that each school had a whole-school overview and for the study to have a global perspective of each center. Similarly, we worked together with school leaders and teachers with the aim to increase students’ PA levels during the school day by implementing the three arms of the intervention: PAL, AB, and AR (see Figure 2).

**Figure 2 fig2:**
[figure not shown]
Creating active schools framework for MOVESCHOOL. Source: adapted from Daly-Smith et al. (26).

#### Physically active lessons component

2.3.1

The PAL intervention consisted of integrating PA into academic lessons in different subjects that were typically sedentary. One subject was selected for each week of the intervention. Out of the total number of lessons taught per week in the selected subjects, one lesson per week for 29 weeks was dedicated to the PAL intervention. Each of the PAL was developed outdoors during the intervention. The PAL sessions lasted 60 min and were fully designed with tasks that incorporated PA throughout the session. According to the results of a pilot study we conducted in a previous study (39), participants spent an average of 29.78% of the PAL session time in MVPA. Since the activities of PAL implemented in both studies was similar, we expect PA intensities also to be similar. The teacher assigned to this intervention group, who has been trained beforehand, supervises the implementation of the strategies in their academic lessons with the constant support of the research team. Before each PAL lesson, the research team and the teacher met to determine the specific content to be covered and to jointly develop the activities to be included in the lesson. Examples of PAL activities can be found in Grao-Cruces et al. (40) and here.

Teacher training was conducted in the month prior to the start of the intervention. It consisted of two 60 min workshops, led by the members of the research team, aimed at providing teachers with a foundation for implementing PAL in their teaching. The training covered: theoretical foundations of PAL, main characteristics of PAL, applicability and examples of PAL in secondary school subjects.

#### Active break component

2.3.2

The AB intervention consisted of two daily ABs in a normal academic lesson. The timing of the AB was coordinated with the school management team, with one AB before recess and the other after recess. It was important that no AB are scheduled during PE classes or the lesson immediately following PE. This precaution ensured that the impact of the AB is not solely attributed to the PA that took place in the preceding PE lesson.

In order to facilitate the implementation of the AB, teachers used an adapted version of the “EUMOVE Active Breaks Platform,” a digital platform specifically designed for the implementation of AB (41). Therefore, before developing the intervention, the ABs were programmed in this platform. In this way, only the teachers who would be teaching the class at the time scheduled for the intervention were able to access the platform and start the programmed ABs. An example of an AB can be found here. This innovative tool made it possible to easily and quickly programme different types of AB, playing with variables such as PA duration or intensity. According to Daly-Smith et al. (14), each AB lasted 5 min and consisted of 4 different exercises, divided into 2 sets (4 rounds each) of 20 s of work and 10 s of rest. Finally, a cool-down consisting of deep breathing is performed. The activities selected for each AB included aerobic and strengthening activities (i.e., squats, lunges, jumps or skipping).

Teachers were given access to the platform and were tasked with delivering the AB according to the schedule provided by the research team. Throughout the intervention, students followed the instructions of an avatar who facilitates the session through the platform. To ensure optimal use of the platform, the research team provided extensive training and ongoing support to the teachers. During the initial phase of the intervention, the research team provided teachers with hands-on guidance for the first 2 weeks to ensure seamless integration of the AB and to address any queries or concerns that may arise. This support is designed to familiarise teachers with the platform and give them the confidence to deliver the AB.

#### Active recess component

2.3.3

The aim of this component of the intervention was to increase levels of PA during school recess. To promote PA during school recesses, three strategies were developed: (i) environmental modification; (ii) free availability of sports equipment; and (iii) structured recess. Environmental modification provided a greater number of spaces where students could be active during playtime. The playground space was divided into zones and configured with different activities to vary space usage. The students were able to access to sports equipment in order to encourage the practice of PA during recess. Loose equipment had the advantage over fixed equipment or changes in infrastructure because it can be modified regularly. Structured recess includes organizing sports competitions and activities led by teachers. All of this is prepared by the research team together with the school’s PE teachers, and during its implementation, it was supervised by the technician along with the teachers assigned to recess duty.

#### Control group

2.3.4

During the 29-weeks of intervention period, schools belonging to the control group received the standard academic lessons without methodological modification or inclusion of PA that could alter the usual levels of PA during school hours.

### Implementation strategies

2.4

Several implementation strategies were used to ensure the success of this intervention programme. The primary approach was to assign a technician to each school in the experimental group. These technicians oversaw the day-to-day running of the project and maintained regular contact with the research groups and their counterparts in other schools. This process facilitated rapid decision-making on matters that required immediate attention or did not require a full meeting of the researchers. In addition, these researchers maintained ongoing communication with the teaching staff and school management teams at the experimental centers. Another implementation strategy involved providing training to teachers for the implementation of PAL, AB, and AR by the research team. The technicians assigned to each school were responsible for daily monitoring to ensure fidelity and/or guarantee the proper modification of any of the components in case they needed to be adapted. Fidelity was monitored through observation, direct questions to the teachers, automatic registration on the AB platform, and attendance lists for classes.

Finally, another important implementation strategy involved structured meetings at different stages of the intervention: (i) an initial meeting of the school management team with the research group to introduce the study and coordinate its development; (ii) an introductory meeting of the principal investigator with the participating teachers to present the project and coordinate its progress; (iii) regular meetings of the principal investigator with the participating teachers to evaluate and monitor the process; (iv) a final meeting of the school management team with the research group to conclude the project.

### Measures

2.5

Participants were assessed at baseline (October 2023) and post-intervention (May 2024). Post-intervention measure of accelerometers-based variables were assessed during the last weeks of intervention, due to the characteristics of the indicators. To minimize variability in assessments, all measurements were conducted in schools by researchers who have received prior training.

#### Primary outcome measures

2.5.1

##### Physical activity and sedentary time

2.5.1.1

The Actigraph device (Actigraph GT3X+, Inc., Pensacola, FL, United States) was utilized for assessing PA at different intensities (light, moderate and vigorous) and sedentary time throughout the entire day. Participants were instructed to wear the monitor on their non-dominant wrist for eight consecutive days. Participants were advised to wear the accelerometer throughout the day (including sleeping time), except during aquatic activities or situations where exposure to water is possible. The screening and data collection procedures adhered to established protocols employed in previous research involving adolescents populations (42). Data will be extracted and analyzed using the GGIR package. Inclusion criteria for the analyses consist of: (i) a minimum of 3 valid weekdays of data and at least 1 valid weekend day of data; (ii) a minimum recording duration of 10 h per day (42, 43). The power analysis is performed based on MVPA during the school day, as it is the main variable of the study.

Additionally, to gather information on screen time throughout the day and the devices used, screen time was assessed using the specific items of the Youth Leisure-time Sedentary Behaviour Questionnaire (YLSBQ) (44). This questionnaire assessed the amount of recreational time per day spent on television, video games, computers, tablets, and smartphones, separately during weekdays and weekends. The student must choose whether they spend “0 min”, “30 min”, “1 h”, “2 h”, “3 h”, “4 h” or “5 h or more” per day on each of these behaviours.

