Analyzing previous studies on interventions for promoting PA in schoolchildren (28–32), it is observed that a large part of these implement a single PA component (e.g., only PAL). Most single-component interventions in schools have shown limited or insignificant post-intervention effects (31, 32). Additionally, the possible low quality of existing systematic reviews, meta-analyses, or the studies included in them limits the ability to draw firm conclusions (32). Despite the limited evidence, multicomponent school-based interventions (targeting two or more components, such as PAL, AB, active commuting, etc.) have been proposed as one of the most promising approaches to promote PA in schools (32–35). However, systematic and meta-analyses examining the effects of multicomponent interventions show inconclusive results and generally small effects (36, 37). Evidence for these types of interventions on variables such as executive functions or academic performance is weak.

On the other hand, most of these multicomponent interventions have been carried out in primary schools (32), and few in secondary stage, with inconclusive effects on PA levels (36, 37). Therefore, there is a need to conduct studies that focus on the secondary level and test multicomponent interventions, as they promise greater effects on PA levels, and all that this entails.

Starting from the fact that this work is a protocol, its aim was to describe the methods and rationale of the MOVESCHOOL study, aimed to examine the effectiveness of a multicomponent school-based intervention on PA levels, sedentary time, HRPF, executive functions, academic indicators (school engagement, learning perception, academic performance and mathematical fluency), psychological health markers and motivational variables in adolescents. A secondary objective was to describe the methods used to evaluate the perception of school leaders, teachers and students (perceptions, limitations, strengths, areas for improvement, perceived benefits, enjoyment, motivation, training needs, fidelity and sustainability) about the intervention. Based on previous studies, this study hypothesized that participants in the experimental group, compared to those in the control group, would show higher PA levels during the school day, improved HRPF, executive functions, academic performance, psychological health, and motivation, as well as a reduction in sedentary time during the school day.

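### One accelerometer inclusion rule, with a compulsory weekend day, governs all analyses, so students with full school-hours data are dropped from the main outcome, school-day MVPA

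*Protocol article*

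**What the plan says.** Section 2.5.1.1 of the protocol article (Physical activity and sedentary time) gives one rule, introduced by the words "Inclusion criteria for the analyses consist of". It has two parts: "a minimum of 3 valid weekdays of data and at least 1 valid weekend day of data", and "a minimum recording duration of 10 h per day". The device is worn on the wrist for eight consecutive days, and students were told to "wear the accelerometer throughout the day (including sleeping time", with an exception only around water.

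The sentence straight after the rule reads: "The power analysis is performed based on MVPA during the school day, as it is the main variable of the study". The sample size paragraph under Figure 1 agrees, referring to "our main variable, MVPA time during the school day". The hypothesis at the end of the Introduction uses the same window: the experimental group "would show higher PA levels during the school day", and sedentary time during the school day would fall.

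Section 2.5.1.1 also measures activity and sedentary time over the entire day, and these measures stand under the primary outcome heading (2.5.1). Nothing in the article exempts the school-day outcomes from the weekend condition.

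**The concern.** The rule suits a whole-week estimate of activity but is the only one stated, so it also decides who enters the analysis of a school-hours outcome. No weekend minute enters a school-day value. A student can therefore have every school hour recorded at both waves and still be excluded for not wearing the device on Saturday or Sunday.

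Two things are at stake. The first is precision, because observed values of the main outcome are thrown away. The second is selection. Students remain in the analysis partly according to their weekend compliance, and section 2.2 describes a nonequivalent control group design, so randomisation does not balance the groups at the outset.

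A lesser point concerns the 10 h criterion. It sets an amount of recording per day without saying when in the day it must fall. A weekday can meet it with little or no wear during school.

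**Working it through.** The plan gives no figure for losses under this rule, so there is nothing to reproduce. The check is one of logic, followed by an illustration of size.

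**Weekend condition, by the text.** Take a student with five complete school days at each wave and no valid weekend day. At least 3 valid weekdays: met. At least 10 h on those days: met. At least 1 valid weekend day: not met. The student is excluded although the school-day outcome is fully observed.

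**Size of the loss.** Inputs:
- 800 planned and 15% dropout (sample size paragraph): 800 × 0.85 = 680 retained.
- Two weekend days per wave. Eight consecutive days starting on a weekday contain exactly two; a weekday start is assumed.
- Each weekend day valid with probability p = 0.7 to 0.9, independently across days and waves. This is assumed; the article gives no figure.
- A student needs valid data at both waves, as in a complete-case repeated measures ANOVA (the Abstract names that method; complete cases are assumed).

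Failure at one wave = (1 − p)². Failure at either wave = 1 − [1 − (1 − p)²]².

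| p | One wave | Either wave | Of 680 | Left |
|---|---|---|---|---|
| 0.9 | 0.01 | 1 − 0.99² = 0.020 | 14 | 666 |
| 0.7 | 0.09 | 1 − 0.91² = 0.172 | 117 | 563 |

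Independence is a convenience. If the two days of a weekend tend to fail together, the one-wave figure rises, in the extreme to 1 − p (10% to 30%). If the same students fail at both waves, the either-wave figure falls towards the one-wave figure.

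**Effect on power.** The article does not state the test, the effect metric or the correlation behind its sample size, so one variant was assumed: group-by-time interaction, 2 groups × 2 times, f = 0.1, correlation ρ = 0.5, α = 0.001, no clustering by school, noncentrality λ = f² × N × 2 / (1 − ρ). At N = 680, λ = 0.01 × 680 × 2 / 0.5 = 27.2.

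| N | Power |
|---|---|
| 680 | 0.97 |
| 646 | 0.96 |
| 612 | 0.95 |
| 550 | 0.92 |
| 435 | 0.80 |

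The range 563 to 666 therefore corresponds to power between 0.92 and 0.97. Power falls to 0.80 only at a loss of 20% at each wave (680 × 0.8² = 435). These levels depend on the variant: with ρ = 0.3, power at 680 is already 0.86. They show the relative cost of the exclusions, not the true power of the study.

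**10 h criterion.** The length of the school day is not given; assume 5 to 7 h. In a 24 h recording, 24 − 7 = 17 to 24 − 5 = 19 h lie outside school, so 10 h can be reached with no school-hours wear. If only waking wear counted (15 to 16 h awake, assumed), 15 − 7 = 8 to 16 − 5 = 11 h lie outside school. At the lower end, 10 − 8 = 2 h of a 7 h school day would be enough. Either way the criterion does not secure wear in the window that matters.

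**The case against.** The best defence is that the rule is sensible for what is also measured. Whole-day activity and sedentary time stand under the primary heading, and a weekend day is a reasonable requirement for them. That stands. The fault lies only in using it as the sole rule for the school-day outcomes, and those whole-day measures should not be treated as secondary.

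A second defence is that an article condenses a fuller protocol, where a school-hours wear threshold may be found. This weakens the 10 h point, which rests partly on what the article leaves out. It does not touch the weekend condition, which is written out explicitly.

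A third defence is that the loss is assumed and may be small. Wear is continuous, the rule is the same in both groups, and the 15% dropout allowance may already cover unusable recordings. The count of 14 to 117 also supposes that those students meet every other criterion. All of this stands and limits the severity.

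Three stronger readings are tempting and are not supported:
- A reader might infer that weekdays without school-hours wear do enter the main analysis, with values supplied by the software. The text permits such days, but their frequency is unknown, and the article says nothing about filling missing segments.
- A reader might infer that the main result is biased. No passage shows that weekend compliance differs between groups or relates to change in school-day MVPA.
- A reader might infer that three valid weekdays misstate the contribution of the weekly active lesson. At 29.78% of 60 min (section 2.3.1), or 17.9 min, that lesson contributes 17.87 / 5 = 3.6 min a day over five days, but 0 or 17.87 / 3 = 6.0 over three. If missing days are unrelated to the lesson day, the expected value is 0.6 × 5.96 = 3.6. That is noise, and it comes from the three-weekday minimum rather than from the weekend or 10 h criteria.

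**Conclusion.** The concern holds for the weekend condition. Followed as written, the plan excludes students with complete school-hours data from the analysis of its main variable, for lacking data that cannot inform that variable. Precision is lost needlessly and the analysed group is selected on weekend compliance. How many students this affects cannot be derived from the article. With two weekend days per wave, each independently valid with probability 0.7 to 0.9, it is about 2% to 17% across the two waves, and the effect on power is modest.

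The 10 h criterion does not ensure school-hours wear. This is a supporting point of unknown practical weight.

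Severity is moderate, and the change is a cheap improvement. The material does not show that the study is underpowered or its result biased because of this rule.

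**What to change.** For school-day MVPA and school-day sedentary time, drop the weekend-day condition. Define a valid school day by wear within that school's timetabled hours, and require a minimum number of such days per wave (for example 3). Fix the wear threshold before outcome data are examined.

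Keep the present rule for the whole-day and whole-week accelerometer outcomes, which are also listed as primary. Report the school-day result under the present rule as a sensitivity analysis; section 2.6 already foresees sensitivity analyses in general terms. Report how many students each rule excludes, by group and wave, so that the selection can be seen.

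No new data are needed. Section 2.5.1.1 puts data extraction in the future tense, so the change affects processing settings only. The cost is that two validity rules must be described and reported, and the school-day and whole-week analyses will rest on somewhat different students.
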